### Cognitive functional therapy

CFT will be conducted once a week in individual sessions lasting approximately 60 minutes over 8 weeks. The procedures of each session will be documented by the therapists for every participant. The therapists administering CFT will undergo specific training that includes: (1) a minimum of 106 hours of CFT training with an experienced CFT tutor, and (2) analysis of videos of the therapists implementing the CFT approach by an experienced physiotherapist. CFT is structured around creating a strong therapeutic connection, using active listening alongside a motivational interviewing style that is open, reflective, and non-judgmental. This approach provides validation and employs specific strategies to reinforce the therapeutic bond between therapist and patient [68,20]. The CFT will contain:

i) Anamnesis will be conducted to evaluate the degree of pain focus, pain coping strategies, stress response, and its connection to pain their beliefs regarding pain, as well as any history of anxiety and depression, and their expectations and goals regarding the management of the shoulder pain [69].ii) Physical examination will be conducted to identify the individual’s primary maladaptive behaviors (e.g., pain-provoking, feared and/or avoided movements and/or functional tasks), that can be classified into movement impairments and control impairment. Movement impairments are characterized by movement restriction in the direction of pain and control impairments are impairments of functional control of postures and movements that can be associated with aberrant movement and postural control or muscle activity [26,70,71]. Subsequently, an approach focused on the potentially contributing factors to pain will be performed, covering the three following components [19,26]:i) Making sense of pain is a reflective process that incorporates a patient’s story and relevant life experiences, alongside their behavioral exposure outcomes. This process helps them reach a new understanding of their pain and also increases self-efficacy to accomplish personal goals.

Developing a timeline of the pain history, along with recalling biopsychosocial factors that may have contributed to the onset and persistence of symptoms, can help make sense of their chronic pain and disability. Listening to the patient’s history is important to understand the context, location, and nature of their pain, assess their level of disability, beliefs, coping mechanisms, physical and lifestyle factors, as well as their goals and values.

The therapeutic alliance is strengthened through empathy, mirroring, reflective listening, and reinforcement of adaptive behaviors. Patients become aware of circumstances that lead to pain flare-ups, helping them recognize and explore coping strategies. Afterward, a summary of the discussion is reviewed with the patient.

ii) Exposure with control is a process of behavior change. This approach allows individuals to gradually resume meaningful activities without increasing pain or distress. It encourages viewing the pain experience as a hypothesis to be tested through behavioral experiments, making use of the pain experience whenever feasible. For instance, “raising my arm will increase my pain.” This is an experience where learned associations between threatening tasks and increased pain or harm can be corrected, and new “safety” associations are created. This strategy is based on the assumption that expectancy violation – the discrepancy between expectation and experience – is helpful for new learning.

Some individuals focus on reducing pain during task performance, while others prioritize engaging in feared or avoided tasks without causing harm. In this approach, sympathetic responses and safety-seeking behaviors that arise during painful, feared, or avoided tasks are specifically managed to create a contrast between the expected and actual pain experience. An example of prior individual expectation could be: “I expect my pain will increase if I raise my arm repeatedly.” Individual experience: “When I relax, breathe, and raise my arm without protecting it, my pain does not get worse – it improves.”

The practice of exposure with control improves relaxation before engaging in activities, reducing protective behaviors, and increasing body awareness and control. This approach helps individuals perform daily tasks more naturally. For example, calmly lifting the arm and adjusting movements to avoid unnecessary guarding can lead to a constructive experience through safety learning.

iii)  Lifestyle change aims to help patients embrace a healthy lifestyle. Strategies for altering unfavorable lifestyle behaviors are discussed as part of making sense of pain. Physical activity is tailored to individual preferences and aligned with personal goals, taking into account factors such as cost, accessibility, and social involvement to encourage lasting behavior change. Sleep deficits related to poor sleep hygiene are managed by creating a consistent daily routine and minimizing electronic device use in bed. Pain, anxiety, and stress-related disturbances can be managed with relaxation techniques like guided mindfulness and consistent physical activity. When difficulties with bed movement and positioning are identified, specific training is offered to promote more relaxed and comfortable rolling and positioning techniques [19,21,26].

### Therapeutic exercises group

Individuals assigned to this group will be treated twice a week for 8 weeks. Each session will last approximately 40–60 minutes and will consist of bilateral stretching and strengthening exercises targeting the scapulothoracic and glenohumeral muscles, which are commonly associated with shoulder pain [10,11,72]. In addition, the therapist will manage symptoms by applying ischemic compression for 90 seconds, or until symptom reduction, on latent or active trigger points in the deltoid and upper trapezius, as needed. Stretching exercises will be performed in three sets of 30 seconds, with 10 seconds of rest between sets, and an intensity of maximum stretch without pain, targeting the following muscles:

i) Upper trapezius: The individuals will be instructed to flex the neck, side-bend away, and rotate towards the side to be stretched, then force down the arm on the side being stretched. This movement can be assisted and maintained during the maneuver by the contralateral hand [38,39,73].ii) Pectoralis minor: Individuals will be positioned with 90º of shoulder abduction, 90^o^ of elbow flexion, and forearm on the corner of a wall. Then, the individuals will shift the trunk forward and rotate opposite to the side being stretched [74].iii) Posterior shoulder region: the individuals will be positioned in supine and the therapist will stabilize the scapula placing one hand on the lateral edge of the scapula, and with the other hand, the therapist will perform shoulder horizontal adduction [75].

Strengthening exercises will be performed using dumbbell or elastic resistance bands (Theraband ®) with 4 progressive levels of resistance: red (medium), green (heavy), blue (extra heavy), and gray (super heavy). The starting level of resistance will be adjusted for each individual based on their strength and ease of performing the exercise correctly. The individuals will perform three sets of 10 repetitions, with one minute rest between sets, for each strengthening exercise. The progression of resistance will be regulated individually using the 11-point rating of perceived exertion (RPE) scale according to the corresponding muscle being exercised [76], validated for quantifying the intensity of resistance exercise [77]. The scale values range from 0 (“no effort”) to 10 (“maximum effort”) and participants will be instructed in advance on how to report their exertion using the scale and will report after every set of exercises [78]. If self-reported pain occurs during exercise, the exercise will continue as long as the pain does not worsen or hinder proper execution. Otherwise, the therapist will reduce the resistance. The individuals will perform the exercises at a moderate intensity (PSE score between 3–5 points) and the resistance will be adjusted by changing the length or the elastic resistance. The strengthening exercises will be as follows [10,38,39,73]:

i) Lower trapezius - Prone extension exercise: The individual will be positioned in the prone position, with the shoulder in 90º flexion and neutral rotation, and extended elbows. Afterward, the individuals will perform the shoulder extension movement to the neutral position (arm at the side of the body) holding a dumbbell [79,80].ii) Middle trapezius - Horizontal abduction exercise with lateral rotation: The individual will be positioned in the prone position, with the shoulder at 90º flexion and external rotation, and extended elbows. Then, the individuals will perform the horizontal abduction movement holding a dumbbell [80]iii) Serratus punch exercise: The individual will be positioned in the supine position, with the shoulder at 90º flexion, elbows extended and will perform the shoulder protraction holding a dumbbell [81].iv) Shoulder external rotators: The individual will be positioned standing, with the elbow at 90° flexion and shoulder adducted and internally rotated. Then, the individuals will be instructed to perform external rotation against elastic resistance [80,82].v) Shoulder internal rotators: The individuals will be positioned standing, with elbow at 90° flexion and shoulder adducted and laterally rotated. Afterward, the individuals will be instructed to perform the internal rotation against elastic resistance [80,82].

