i) Pressure Pain Threshold (PPT) is the minimum pressure that triggers the first pain sensation. PPT will be measured by a digital pressure algometer (AlgoMed ®, Hӧrby, Sweden) with a 1 cm^2^ circular rubber probe tip and a pressure rate of approximately 40 kPa/s, following established protocols [56,9]. Participants will be seated comfortably and instructed to maintain trunk stability during the test. The PPT test will be performed at the acromion and muscle bellies of the deltoid muscle belly (near the inferolateral insertion) and upper trapezius (halfway between the C7 spinous process and acromion process) on the affected or most affected side. PPT of a distant site from the shoulder (tibialis anterior) will also be assessed to investigate central sensitization [9]. The side for the tibialis anterior assessment will be randomly determined using a computer-generated randomization list (randomization.com). The non-painful side will be used as the remote site for participants with lower limb pain. A computer-generated randomization list will also determine the order of testing regions, stored in sealed opaque envelopes to be opened immediately before testing begins. Each site will be tested three times, with a 30-second interval between repetitions, and the average will be considered for analysis. Participants will undergo familiarization with the procedure at the lateral epicondyle. The PPT has been considered reliable, with ICC coefficients ranging from 0.82 to 0.97[58].ii) Temporal summation refers to increased perceived pain from repetitive nociceptive stimuli at the same site, which is related to the modulation mechanism occurring in second-order sensory neurons in the spinal cord [59,60]. The temporal summation will be measured at the deltoid and tibialis anterior in the same position used for the PPT testing, with a 2-minute interval between testing regions. Sequential stimulation will involve 10 pressure stimuli at the pre-established PPT level, with a one-second interval between stimuli [9,61]. Each pressure increment will be approximately 40 kPa/s [9,61]. After the first and tenth stimuli, participants will rate their pain intensity using the NPRS. The temporal summation will be quantified by subtracting the pain intensity rating for the first stimulus from the pain rating for the tenth [9,61].iii) Conditioned Pain Modulation (CPM) refers to the central nervous system’s ability to inhibit pain through mechanisms related to endogenous descending inhibition [9,62]. CPM will be assessed using the cold pressor test as the conditioning stimulus and PPT as the test stimulus. Cold pressor pain induces an effective CPM response when combined with the test stimulus of the PPT [63,64]. CPM will be evaluated in the same position used for the PPT. The participant will immerse their hand up to the wrist of the non-painful (or least painful) side [9] in ambient temperature water (22ºC) for 1 minute to standardize hand temperature [65]. Afterward, the individual will immerse the same hand in a cold-water bath (8°C) for 2 minutes. PPT at the deltoid of the affected (or most affected) side will be assessed at baseline, during immersion (after 30, 60, and 90 seconds), and after immersion (immediately post-withdrawal and at 30 and 60 seconds after withdrawal). Participants will rate their pain intensity on an 11-point NPRS every 30 seconds from immersion until hand withdrawal, and 30 and 60 seconds after withdrawal [66]. Conditioned pain modulation will be calculated by subtracting the PPT of the deltoid from PPT measures during and after CPM [62,64].

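### Deltoid and upper trapezius sensory results are labelled central, but only the exercise arm may have those muscles compressed, so a difference there cannot by itself be reported as a central effect

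*Protocol article*

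**What the plan says.** **Treatment.** In the section Therapeutic exercises group, sessions run twice a week for 8 weeks, and the therapist may add a manual technique: "applying ischemic compression for 90 seconds, or until symptom reduction, on latent or active trigger points in the deltoid and upper trapezius, as needed". The section Cognitive functional therapy describes an interview and a physical examination, after which "an approach focused on the potentially contributing factors to pain will be performed, covering the three following components". Those components are making sense of pain, exposure with control, and lifestyle change. No manual technique is listed among them.

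**Testing.** Under Central pain processing:
- PPT, shoulder sites: "The PPT test will be performed at the acromion and muscle bellies of the deltoid muscle belly (near the inferolateral insertion) and upper trapezius".
- PPT, remote site: "PPT of a distant site from the shoulder (tibialis anterior) will also be assessed to investigate central sensitization".
- Temporal summation: "The temporal summation will be measured at the deltoid and tibialis anterior in the same position used for the PPT testing".
- CPM: "PPT at the deltoid of the affected (or most affected) side will be assessed at baseline, during immersion". No other CPM test site is named.

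**Label and aim.** Table 2 groups PPT, temporal summation and CPM as central pain processing measures and does not separate shoulder sites from the remote site. The Introduction makes central pain processing one of the aspects compared between arms and expects CFT to improve it more.

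**The concern.** Pressure applied to a muscle as treatment, and pressure applied to the same muscle as a test, can interact without any change in central processing. If compression makes the deltoid or trapezius less tender, thresholds there rise in the exercise arm only; if it leaves them sore, thresholds fall in that arm only. In the first case a central benefit of CFT could be hidden, or a central benefit of exercise claimed. In the second, CFT could look better than it is.

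At stake is the mechanistic conclusion. With every site under one central heading, nothing in the document stops a local difference from being reported as a central one.

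**Working it through.** **1. The plan's own figure.** The sample size is not part of this point, but it supplies the number of completers used in step 3. With the protocol's formula and r = 1, n = 2 × (1.960 + 0.842)² × 24.6² / 18² = 29.3, rounded up to 30 per arm. Then 30 / 0.85 = 35.3, rounded up to 36 per arm, 72 in total. The stated figure reproduces.

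**2. Treated muscles against tested sites.**

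| Measure | Sites tested | In a compressed muscle | Elsewhere |
|---|---|---|---|
| PPT | acromion, deltoid, upper trapezius, tibialis anterior | 2 of 4 | acromion, tibialis anterior |
| Temporal summation | deltoid, tibialis anterior | 1 of 2 | tibialis anterior |
| CPM | deltoid | 1 of 1 | none |

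Of the 7 measure-by-site combinations, 4 lie in a compressed muscle and 3 do not. One of those 3, PPT at the acromion, is still a shoulder site. That leaves 2 remote combinations: tibialis anterior PPT and tibialis anterior temporal summation.

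**3. How much a local shift could matter for raw PPT.** The documents give no PPT standard deviation and no local effect, so everything in this step is assumed: 30 completers per arm, SD of 100 to 150 kPa, a purely local one-arm shift of 20 to 50 kPa, one time point, unadjusted two-sided 5% test, normal approximation.

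SE = SD × √(2/30), which is 25.8 kPa for SD 100 and 38.7 kPa for SD 150. The chance of a nominally significant difference is P(|Z + shift/SE| > 1.96).

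| Shift | SD 100 | SD 150 |
|---|---|---|
| 0 kPa | 5% | 5% |
| 20 kPa | 12.1% | 8.1% |
| 50 kPa | 49.1% | 25.2% |

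These figures apply to deltoid or trapezius PPT only. They are the chance of seeing a local difference when there is no central one. They are not a false-positive rate for the comparison of packages, because a local change produced by the exercise package is a real difference between packages.

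**4. How much reaches CPM and temporal summation.** CPM is the change from the deltoid PPT within the session, and temporal summation is the tenth rating minus the first, at the participant's own PPT. A constant shift in threshold therefore partly drops out of both. It need not drop out entirely. If inhibition were proportional to the threshold (assumed here at 20%), a deltoid PPT of 250 kPa would score 0.20 × 250 = 50 kPa and one of 300 kPa would score 0.20 × 300 = 60 kPa. A local shift of 50 kPa would then appear as 10 kPa of CPM with identical central function. For temporal summation, a changed threshold changes the physical stimulus delivered. The documents do not allow either effect to be sized.

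**The case against.** The strongest reply is that the protocol already contains the control. It tests the tibialis anterior for PPT and temporal summation, and it names central sensitization as the reason for the remote PPT. Nowhere does it say that shoulder-site results alone will be taken as central. A reader might infer from Table 2 that they will be; the text supports only that they can be. This stands, and the point is worded accordingly.

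Other parts of the reply also stand:
- The acromion is not listed for compression, so the tibialis anterior is the only remote site, not the only uncompressed one.
- Within-session differencing partly protects CPM and temporal summation.
- The range in step 3 is assumed and covers raw local PPT only. It also ignores the planned mixed models with Bonferroni adjustment.
- Compression is given as needed, its side and exact points are not stated, and the same arm also stretches and strengthens shoulder muscles. Some local effect is inherent in comparing exercise with CFT.
- Outcomes are also assessed at week 12, four weeks after treatment ends, when short-lived soreness would not be expected to drive results.

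Two stronger readings should be set aside. One is that the missing interval between a session and sensory testing, or the missing log of compression, is a defect; an article commonly leaves such detail to the full protocol. The other is that CPM must move to the tibialis anterior; that is a trade-off against comparability with earlier shoulder studies.

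The reply does not remove the inconsistency of labels. The measurement text gives the remote PPT site the task of investigating central sensitization, while Table 2 puts the shoulder sites under the same central heading.

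**Conclusion.** The point holds as one of labelling and interpretation of secondary outcomes. Four of the 7 measure-by-site combinations lie in muscles that only the exercise arm may have compressed, including the only CPM site. A between-arm difference at the deltoid or trapezius cannot by itself be reported as a central effect.

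A reader might go further and infer that the randomized comparison is biased. The documents do not support that: compression is part of the exercise package, so the comparison of packages remains valid at every site, and pain intensity, SPADI and the sample size are unaffected.

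The overlap of sites is read directly from the protocol. The size of any local effect is not; the 8% to 49% range rests wholly on the assumptions in step 3 of the working.

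**What to change.** Amend the outcome description and Table 2 as follows; neither treatment changes.

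1. Base between-arm conclusions about central pain processing on tibialis anterior PPT and tibialis anterior temporal summation. Both are already collected. The protocol itself gives the central rationale for the PPT; extending it to temporal summation at the same site should be stated.
2. Report PPT at the acromion, deltoid and upper trapezius, and temporal summation at the deltoid, separately as local mechanical sensitivity.
3. State that CPM is tested at the deltoid only, has no remote test site, and so cannot fully separate local from central effects.

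The cost is wording: no new visit, device, test site or data. The small downside is that fewer measures support a claim about central processing.

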### Data management

Information regarding recruitment, participant characteristics, study completion, dropout rates, and outcome measures will be securely stored at the Universidade Federal da Paraíba. To protect individuals’ privacy and data, identifiers will be stored separately. Data will be entered into a computer software program (Excel™, Microsoft, 2016) and cross-checked on a weekly basis by an assistant, using standardized coding to maintain participant confidentiality. Access to the database will be restricted to the primary investigators. There are no contractual agreements limiting investigator access.

### Data analysis

Statistical analysis will be conducted using the Statistical Package for the Social Sciences (SPSS) version 24.0 or a more recent version (SPSS Inc., Chicago, IL). Continuous data will be summarized as means ± standard deviation (SD) and 95% confidence intervals (CIs). Data normality will be assessed through visual inspection of histograms and the Shapiro-Wilk test. The analysis will adhere to the intention-to-treat principle. Between-group differences (treatment effects) and their corresponding 95% CIs will be computed using linear mixed models with Bonferroni adjustments. If non-normality of the data is identified, transformations will be performed as needed or generalized linear mixed models will be considered. Fixed effects will include group, time, and the group-by-time interaction. Random effects will account for individual variability. A significance level of 0.05 will be applied for all statistical tests.

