### Sample

The study will include adults aged between 18 and 60 who report shoulder pain lasting at least 3 months. They should rate their shoulder pain 4 or higher on the 11-point Numerical Pain Rating Scale (NPRS) over the past week [32], and high level of disability (Shoulder Pain and Disability Index score ≥ 47) [33,34] or moderate irritability according to Staged Approach for Rehabilitation Classification: Shoulder Disorders (STAR–Shoulder) [35,36].

Non-inclusion criteria will be apply to individuals with: a history of fracture or surgery of the clavicle, scapula and/or humerus; surgical stabilization or repair of the rotator cuff; a history of dislocation, instability (positive Groove Sign or Seizure Test) and/or rotator cuff rupture (positive Arm Drop Test); adhesive capsulitis verified by the presence of pain with gradual onset associated with stiffness and reduced passive and active mobility; reproduction of pain in the shoulder that radiates to the entire upper limb, ongoing pregnancy; tingling or numbness in the upper limb or any other symptom in the upper limb during tests on the thoracic or cervical spine (Positive Spurling Test); systemic disease or neurological condition that can alter muscle strength and sensitivity, such as fibromyalgia, rheumatoid arthritis, gout, lupus, diabetes and/or stroke; physiotherapy treatment for shoulder pain in the previous 3 months, corticosteroid injection in the shoulder region in the last 3 months, and active treatment for cancer [37–39], impairments in sensation, blood clotting disorders, and/or contraindications to the application of ice.

Individuals with surgeries, fractures, musculoskeletal or neurological conditions preventing them from accessing treatment, or those who received corticosteroid injections in the shoulder region during the treatment or follow-up period will be discontinued from the study.

The sample size was calculated using the SampSize App (https://app.sampsize.org.uk/) and the following formula described by Flight et al (2015) [40]:

$$n=\frac{\left(r+1\right){\left(Z_{1-\beta }+Z_{1-\frac{\alpha }{2}}\right)}^{2}\sigma^{2}}{rd^{2}}$$

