The calculation was based on an estimated mean difference of 18 points [41] (standard deviation of 24.6) [42] in shoulder disability, assessed with Shoulder Pain and Disability Index (SPADI), with a two-tailed significance set at 0.05, power at 80%, and accounting for a 15% dropout, which resulted in 36 individuals per group for a total of 72 individuals. The sample size, calculated based on pain intensity (a mean difference of 2 points and a standard deviation of 2.5 on the NPRS), resulted in a total sample of 48 individuals. Therefore, the sample size calculation for this study was based on shoulder disability.

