### Primary outcomes

#### Numerical Pain Rating Scale (NPRS).

The 11-point NPRS will measure shoulder pain intensity during functional activity involving arm elevation and the highest pain intensity experienced in the past week. The scale ranges from 0 (no pain) to 10 (maximum pain) and is a valid and reliable tool for assessing individuals with shoulder pain (intraclass correlation coefficient - ICC of 0.84) [42,44]. The minimum clinically significant difference (MCID) is a change of 2 points or 30% [45].

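### Normality is judged on the data rather than on model residuals, and an open-ended fallback could take the NPRS and SPADI effects off the points scale used for planning

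*Protocol article*

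**What the plan says.** All of the rule stands in the Data analysis section of the protocol article.

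- Main analysis: "Between-group differences (treatment effects) and their corresponding 95% CIs will be computed using linear mixed models with Bonferroni adjustments".
- Check: "Data normality will be assessed through visual inspection of histograms and the Shapiro-Wilk test".
- Consequence: "If non-normality of the data is identified, transformations will be performed as needed or generalized linear mixed models will be considered".
- Level: "A significance level of 0.05 will be applied for all statistical tests".

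Residuals are not mentioned. No transformation, link function, decision threshold or back-transformed effect measure is named.

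Planning and interpretation are in points. For SPADI, the Sample section states: "The calculation was based on an estimated mean difference of 18 points", with a standard deviation of 24.6. For NPRS it uses 2 points and a standard deviation of 2.5. The NPRS section adds: "The minimum clinically significant difference (MCID) is a change of 2 points or 30" per cent.

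Entry conditions shape the baseline scores. For pain: "They should rate their shoulder pain 4 or higher on the 11-point Numerical Pain Rating Scale (NPRS) over the past week". For disability, the requirement is a SPADI of at least 47 "or moderate irritability according to Staged Approach for Rehabilitation Classification: Shoulder Disorders (STAR–Shoulder"), so a participant can enter with a SPADI below 47.

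**The concern.** There are two difficulties.

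First, the check looks at the wrong object. A linear mixed model assumes normal residuals and random effects, not normal outcome scores. Scores can fail a normality test because of integer scoring, an entry cut, a floor, or a difference between the arms, while the model's estimate of a mean difference remains sound.

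Second, what follows a failed check is left open. A transformed outcome, or a generalized linear mixed model with a non-identity link, changes the quantity being estimated. A coefficient on such a scale cannot be read directly against 18 SPADI points, 2 NPRS points or the MCID in points. The Data monitoring section places the analysis after all data collection, so the scale of a primary effect could be settled once the data are in hand.

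**Working it through.** **The plan's own figure.** The per-arm size is n = 2(z₀.₈₀ + z₀.₉₇₅)²σ²/d². For SPADI this is 2 × 7.849 × 24.6²/18² = 2 × 7.849 × 605.16/324 = 29.3, so 30. With 15% dropout, 30/0.85 = 35.3, so 36 per arm and 72 in total. The stated figure is reproduced. It is expressed in points.

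**What a change of scale does.** The starting values here are illustrative. A fall from 6 to 4 and a fall from 4 to 2 on the NPRS are both 2 points. On a log scale they are ln(4/6) = −0.41 and ln(2/4) = −0.69. On a square-root scale they are 2.00 − 2.45 = −0.45 and 1.41 − 2.00 = −0.59. A single transformed difference therefore has no fixed equivalent in points.

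**How often Shapiro-Wilk rejects at 0.05.** The protocol gives no score distributions, so means and standard deviations are assumptions, with 4,000 simulated samples per scenario.

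- NPRS is a normal score rounded to integers. At baseline only values of 4 to 10 are kept; at follow-up values are bounded at 0 and 10 with no entry cut.
- SPADI is normal with SD 24.6, kept within 0–100.
- Sample sizes are 72 (all), 61 (72 × 0.85 = 61.2), 36 (one arm) and 30 (one arm, evaluable).

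| Score | Assumptions | Rejected at n = 72 | Smaller samples |
|---|---|---|---|
| Baseline past-week NPRS, cut at 4 | mean 4–7, SD 1.5–2.5 before the cut | 100% | 65–100% at 36 |
| The same without the cut | mean 6, SD 1.5–2.5 | 77–98% | – |
| Follow-up NPRS | mean 2–5, SD 2–2.5 | 50–100% | 35–100% at 61; 13–99% at 36; 12–95% at 30 |
| Baseline SPADI, if 47 were a strict cut | mean 45–65 | 75–98% | – |
| Baseline SPADI, half of those below 47 enter through irritability | mean 45–65 | 15–37% | – |
| Baseline SPADI, no cut | mean 45–65 | 8–29% | – |
| Follow-up SPADI | mean 25–45 | 9–98% | 4–68% at 36 |

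Both the entry cut and integer scoring drive the baseline NPRS result. At follow-up the cut does not apply, and the result depends mainly on how close the mean lies to the floor.

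**Scores against residuals.** A second simulation (2,000 trials per setting) used 72 participants and four visits without dropout. It assumed baseline means of 5–7 with SD 2 before the cut, follow-up SD 2.5, correlation 0.4 with baseline, and a treatment effect of 0 or 2 points.

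- Raw baseline NPRS: rejected in 100%.
- Raw week-8 NPRS: 48–100%. At baseline mean 6 it rose from 73% with no effect to almost 100% with a 2-point effect.
- Week-8 residuals within group: 17–91%.
- Within-participant residuals pooled over the four visits, an approximation to the model's residuals: 5–11%.

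The answer thus depends heavily on what is tested. The week-8 row shows that a significance test on residuals can also reject often.

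**Does the untransformed comparison need rescue?** One case was tested: integer NPRS with mean 2, SD 2.5, bounded at 0 and 10, 30 per arm, no true difference, 5,000 repetitions. The two-sample t-test rejected in 0.045 of them, against a nominal 0.05.

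**The case against.** A reader might infer that the Shapiro-Wilk test alone decides, that the entry cut makes rejection almost certain, and that the primary effect will leave the points scale in practically every run. The documents do not support that.

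- Histograms are used as well, no p-value threshold is attached to the switch, and the wording leaves both transformation and the generalized model to judgement. A rejection rate is not a switch rate.
- The entry cut acts on baseline past-week NPRS. The NPRS section also measures pain during arm elevation, which has no stated cut, and follow-up scores are not cut.
- SPADI, which set the sample size, has the irritability route. Rejection rates of 75–98% need a strict cut at 47 that the plan does not impose.
- An identity-link generalized model would stay in points, and other fits can often be expressed as differences in means. A ratio from a log model might also be set loosely against the 30% form of the MCID.
- The Blinding section keeps the statistician blind to assignment, which limits choosing a model by its result. No type I error was computed for the test-then-choose procedure, so no inflation is claimed.
- An unseen analysis plan may name the transformation or link, or specify residual diagnostics, and a loose author may write data and mean residuals.

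These points stand and limit the size of the problem. They do not remove it. The published rule names the data as the object of the check and permits a change of scale for the primary outcomes. Discretion without criteria leaves that choice until after data collection. This goes beyond omitted detail, because the step that is stated is poorly aimed.

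**Conclusion.** The concern holds in a limited form. The plan checks normality on the data instead of the mixed-model residuals, and allows the result to lead to an unspecified transformation or generalized linear mixed model for NPRS and SPADI.

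A failed Shapiro-Wilk test is near certain only for baseline past-week NPRS in the full sample. For follow-up NPRS (about 12–100%) and for SPADI it is possible but depends on the assumed mean, spread, sample size and, for baseline SPADI, how many enter through irritability. All these rates rest on assumed distributions.

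The switch is not automatic. If made, it could yield a primary effect not directly comparable with the 18-point and 2-point planning differences or the NPRS MCID. The one floor-affected case tested gives no sign that type I error requires such a switch. It would be too much to say that the trial could then not answer its question, or that its p-values are invalid.

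**What to change.** In the Data analysis section, for NPRS and SPADI:

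1. State that the between-group mean difference in points, with its 95% CI from the linear mixed model, is the primary estimate whatever any normality check shows.
2. Assess the model's residuals, preferably by plots, in place of testing the scores.
3. Keep any transformation, generalized linear mixed model, robust interval or participant-level bootstrap interval as a sensitivity analysis specified in advance, and remove the test-then-transform rule for these two outcomes.

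The cost is a change of wording and one additional sensitivity analysis. Recruitment, assessments and the sample size of 72 are unaffected.
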